#### Statistical analyses

Data will be analysed using an intention-to-treat approach with maximum likelihood imputation of missing values. Analyses will include standard descriptive statistics, Student’s *t*-tests, chi-square, correlation, regression and repeated measures ANOVA (or ANCOVA as appropriate) to examine differences over time. Clinically relevant covariates will be included in analyses. Sub-group analyses based on cancer site and anti-cancer treatment status will be conducted. Investigations into responders and non-responders will be conducted to explore heterogeneity of intervention effect.

Sample size calculations were based on having sufficient power to detect a small effect (*d* = 0.02) in study endpoints. Given the number of planned assessments, correction for multiple testing is required. An alpha level of 0.001 was applied which provides adjustment for up to 50 tests. A priori, 420 participants are required to achieve 80% power at an alpha level of 0.001 (two tailed) to demonstrate a mean paired difference of *d* = 0.02 from pre- to post-program. To ensure sufficient participant numbers at the completion of the Life Now Exercise program, sample size calculations accounted for a 30% attrition rate. Thus the evaluation will be conducted on a sample size of 600 participants.

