### Evaluation

Evaluation of the Life Now Exercise program involves measures of uptake, safety, adherence and effectiveness of the program. These analyses incorporate elements of the RE-AIM (reach, effectiveness, adoption, implementation and maintenance) framework [31]. Evaluation of the effectiveness of the program involves comparisons among pre-program, post-program and 6 months follow-up assessments. The evaluation will be undertaken on a sample of 600 people with cancer participating in the program (refer sample size calculations below) with data collection initiating in 2011 and proceeding until the target sample size is achieved.

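### As worded, maximum likelihood imputation followed by t-tests and repeated measures ANOVA understates the standard errors of pre-post change, so the 0.001 level is not held

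*Protocol article*

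**What the plan says.** The first paragraph of Statistical analyses sets the missing-data method: "Data will be analysed using an intention-to-treat approach with maximum likelihood imputation of missing values". The next sentence lists the analyses, among them Student's t-tests and "regression and repeated measures ANOVA (or ANCOVA as appropriate) to examine differences over time". It names no multiple imputation, no rule for pooling variances and no likelihood-based repeated-measures model.

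The second paragraph sets the error control and the size. On alpha: "An alpha level of 0.001 was applied which provides adjustment for up to 50 tests". On size: 420 participants for 80% power, two-sided, and then "sample size calculations accounted for a 30% attrition rate", which brings enrolment to 600. The Evaluation section sets the contrasts: "Evaluation of the effectiveness of the program involves comparisons among pre-program, post-program and 6 months follow-up assessments". The Discussion acknowledges that there is a single group and no comparator.

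**The concern.** A t-test or ANOVA takes every value in the data set as an observation. If missing post-program values are first filled in from a fitted model, the test counts 600 pairs although only about 420 carry post-program information. Values placed at their predicted mean also lie exactly on the regression line, so the spread of change shrinks while the apparent sample grows. Both effects make the standard error too small.

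Three features of this evaluation make that matter. The within-person change is the whole effectiveness comparison, because there is no control group. The per-test level of 0.001 is the stated protection against multiple testing. And the plan itself allows for 30% attrition. The Effectiveness-objective assessments section adds that the objective measures are taken only before and after the program, so no later measurement can inform a missing post-program value.

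**Working it through.** **The plan's own figures.** 0.05/50 = 0.001 and 420/(1 − 0.30) = 600 both reproduce. The 420 does not reproduce from the printed effect size. With n = ((3.2905 + 0.8416)/d)², d = 0.02 gives 42,687, whereas d = 0.2 gives 427, close to 420. That is a separate matter, and nothing below depends on d.

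**Inputs.** From the article: N = 600, of whom 420 have post-program data, and two-sided alpha 0.001 (critical value 3.2905). Assumed, because the article does not give them: bivariate normal pre/post scores with unit variances, no true change, values missing completely at random, and pre/post correlation r shown over 0.3–0.8.

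**Formulas.** Let n be the number observed and m = 1 − n/N the fraction missing.

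- True variance of the maximum likelihood mean change: (1 − r²)/n + (1 − r)²/N.
- Variance that a paired t-test reports after filling in predicted means: [(1 − m)·2(1 − r) + m·(1 − r)²]/N. An observed difference has variance 2(1 − r); a filled-in one has only (1 − r)².
- SE ratio = √(reported/true). Actual error = 2·[1 − Φ(3.2905 × SE ratio)].

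**Worked case, r = 0.5, m = 0.30.** True: 0.75/420 + 0.25/600 = 0.00179 + 0.00042 = 0.00220. Reported: (0.7 × 1.0 + 0.3 × 0.25)/600 = 0.775/600 = 0.00129. SE ratio √(0.00129/0.00220) = 0.77. Effective critical value 3.2905 × 0.766 = 2.52, so the actual error is 0.012.

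As a sanity check, 600 fully observed pairs would give 2(1 − r)/600 = 0.00167. The filled-in data set, with 180 values missing, reports a smaller variance (0.00129) than complete data would.

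**Over the range of r at 30% missing** (simulation: 60,000 replicates per row)

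| r | true variance | reported variance | SE ratio | error, formula | error, simulation |
|---|---|---|---|---|---|
| 0.3 | 0.00298 | 0.00188 | 0.79 | 0.0090 | 0.0094 |
| 0.5 | 0.00220 | 0.00129 | 0.77 | 0.0117 | 0.0121 |
| 0.7 | 0.00136 | 0.00075 | 0.74 | 0.0150 | 0.0150 |
| 0.8 | 0.00092 | 0.00049 | 0.73 | 0.0169 | 0.0167 |

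**Over the fraction missing at r = 0.6** (simulation: 30,000 replicates per row)

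| missing | SE ratio | error, formula | error, simulation |
|---|---|---|---|
| 10% | 0.92 | 0.0025 | 0.0024 |
| 20% | 0.84 | 0.0059 | 0.0061 |
| 40% | 0.67 | 0.0284 | 0.0297 |

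**Variants at 30% missing.**

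- One random draw per missing value instead of the predicted mean: error 0.0074–0.0107 over the same range of r.
- Direct maximum likelihood with a standard error that reflects the missing data: error 0.0009–0.0012, SE ratio 0.998–1.001.
- Missingness depending on baseline, r = 0.6: filling in predicted means gives 0.0174, and a completers-only t-test gives 0.073. Dropping the imputation and testing completers is therefore not a safe repair.

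**Across 50 tests.** If they were independent, the chance of at least one false positive would be 1 − 0.999^50 = 0.049 as intended. At per-test errors of 0.0094 and 0.0167 it would be 1 − 0.9906^50 = 0.38 and 1 − 0.9833^50 = 0.57.

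**The case against.** The strongest reply is that the article never says that one data set is filled in once. It is a condensed account, and the number of imputations, the pooling rule and the variance estimator commonly sit in a fuller protocol or SAP that is not at hand. The list of analyses is also a general menu that does not tie each test to an endpoint. If full-information likelihood or properly pooled multiple imputation was intended, the level is held.

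This stands as a condition on the size of the problem. It does not remove the problem, because the article states a pairing of methods, imputation followed by complete-data tests, that gives wrong standard errors when followed literally. The text must change under either reading.

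Two further points stand. The 30% is a planning allowance for loss by program completion and applies to post-program values, about 15% of all pre/post values; loss at 6 months is not stated. And a reader might infer that every endpoint is affected. The documents do not support that: the calculation covers pre-post tests on continuous outcomes, and not uptake and attendance proportions, or the cost-effectiveness intervals, which come from Monte Carlo analysis.

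A reader might also infer that the imputation itself inflates the benefit by giving people who left the same change as completers. That does not follow. It is the missing-at-random assumption, which a mixed model shares, and the documents do not show that those who leave do worse.

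**Conclusion.** The point holds as a fault in the stated method, conditional on the literal reading of one filled-in data set. On that reading, pre-post tests on continuous outcomes with missing post-program values report standard errors about 21–27% too small at 30% missing, and the actual type I error is about 9 to 17 times the nominal 0.001. The direction follows from the method. The size depends on the assumed pre/post correlation, on normality and on how much is missing: at correlation 0.6 the error is about 2.4 times nominal with 10% missing and 6 times with 20%. The per-test level meant to cover up to 50 tests is then not held. The article does not establish that single imputation will be used, only that nothing it names would prevent it.

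**What to change.** Replace the imputation sentence and the t-test/ANOVA listing for change over time with one of two methods:

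- a likelihood-based mixed model for repeated measures on all observed data, with time as a factor and no imputation; or
- multiple imputation, with estimates and variances pooled by Rubin's rules.

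If one of these was already intended, say so explicitly.

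Both still assume that data are missing at random, so add one sensitivity analysis in which non-completers' mean change is set to zero. Its effect is easy to foresee: with 30% missing, a completer effect of 0.20 becomes 0.7 × 0.20 = 0.14. That figure illustrates the sensitivity analysis and is not an estimate of bias.

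The cost is revised wording and code, a little more analysis work and wider standard errors. No new data are needed. Precision planned on 420 completers is not lost: at r = 0.5 the direct likelihood variance of 0.00220 is still below the completers-only 2(1 − r)/420 = 0.00238, under the same assumptions.

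### Maximum likelihood imputation is followed by complete-data tests with nothing to carry imputation uncertainty; if it is a single fill-in, standard errors are too small and the 0.001 test is too liberal

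*Protocol article*

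**What the plan says.** All of this comes from the Statistical analyses section of the protocol article.

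- Missing data: "Data will be analysed using an intention-to-treat approach with maximum likelihood imputation of missing values". The number of imputations, the algorithm and the variance method are not given.
- Analysis: after descriptive statistics, t-tests and chi-square, the list ends with "correlation, regression and repeated measures ANOVA (or ANCOVA as appropriate) to examine differences over time". It names no mixed model, direct-likelihood analysis, multiple imputation or pooling rule.
- Significance level: "An alpha level of 0.001 was applied which provides adjustment for up to 50 tests".
- Expected loss: "sample size calculations accounted for a 30% attrition rate", which takes 420 participants with a pre-post pair up to 600 enrolled: "Thus the evaluation will be conducted on a sample size of 600 participants".

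Elsewhere, the section on objective assessments places those outcomes at pre- and post-program only, while the section on patient-reported outcomes places the questionnaires at all time points. The limitations in the Discussion acknowledge that there is no comparison group.

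**The concern.** The sentence names an imputation, and every inferential method after it expects a complete rectangular data set. Read together with the intention-to-treat statement, this most naturally means that the gaps are filled by maximum likelihood and 600 records are then analysed. Two things go wrong in such an analysis. The standard error divides by 600 although at the planned attrition only about 420 post-program values are real. And values placed on the fitted regression line have no residual scatter, so the spread of the change scores shrinks as well.

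This is separate from whether data are missing at random. The point estimate can be unbiased and the standard error still wrong, even under completely random missingness.

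Two features of this study raise the stakes. A test far in the tail, at 0.001, reacts strongly to an understated standard error. And with a single group, the pre-to-post test itself carries the claim of effectiveness.

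**Working it through.** **Inputs from the article.** Enrolled N = 600; attrition m = 0.30, so n = 420 observed post-program values; two-sided alpha 0.001 (critical value 3.2905).

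**Inputs assumed.** Pre-post correlation r from 0.4 to 0.8 (not given in the article); equal pre and post variances, set to 1; missingness completely at random; no true change; one conditional-mean fill-in. Two time points are used. That matches the objective outcomes and simplifies the three-time-point questionnaires.

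**The plan's own figures.** 420/0.70 = 600 and 0.05/50 = 0.001 both reproduce. For the 420, n = ((3.2905 + 0.8416)/d)². With d = 0.2 this gives 427, close to 420; with d = 0.02 as printed it gives 42,687. That discrepancy is a separate matter and does not enter the calculation below.

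**Formulas for the mean change.**

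- True variance of the maximum likelihood estimate: (1−r)²/N + (1−r²)/n
- Variance reported after one conditional-mean fill-in: [(1−r)² + (1−m)(1−r²)]/N
- Actual size: 2[1 − Φ(3.2905 × √(reported/true))]

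**Worked case, r = 0.6.**

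- True: 0.16/600 + 0.64/420 = 0.001790, SE 0.0423
- Reported: (0.16 + 0.7 × 0.64)/600 = 0.608/600 = 0.001013, SE 0.0318
- SE ratio: √(0.001013/0.001790) = 0.752, so the SE is 24.8% too small
- Size: 3.2905 × 0.752 = 2.475, two-sided p = 0.0133

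As a plausibility check, with no missing data at all the variance would be 2(1−0.6)/600 = 0.001333, SE 0.0365. The filled-in analysis therefore claims more precision than 600 fully observed pairs would give.

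**Range, 30% missing, conditional-mean fill-in.**

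| r | SE too small by | Size at nominal 0.001 | Size, 30,000 simulated trials |
|---|---|---|---|
| 0.4 | 22.0% | 0.0103 | 0.0104 |
| 0.5 | 23.4% | 0.0117 | 0.0124 |
| 0.6 | 24.8% | 0.0133 | 0.0135 |
| 0.7 | 26.1% | 0.0150 | 0.0143 |
| 0.8 | 27.4% | 0.0169 | 0.0172 |

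A nominal 95% interval then covers about 85-87% (for example 1.96 × 0.752 = 1.474 at r = 0.6, coverage 86%).

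**Sensitivity to the assumptions.**

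| Case | SE too small by | Size |
|---|---|---|
| 30% missing, r = 0 | 16.3% | 0.0059 |
| 30% missing, r = 0.9 | 28.7% | 0.0190 |
| 30% missing, one random draw, r = 0.4-0.8 | 18.6-22.3% | 0.0074-0.0106 |
| 20% missing, conditional mean, r = 0.4-0.8 | 14.4-18.2% | 0.0049-0.0071 |
| 10% missing, conditional mean, r = 0.4-0.8 | 7.1-9.0% | 0.0022-0.0028 |

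For the single random draw, the true variance gains m(1−r²)/N and the reported variance is 2(1−r)/N.

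**Check of the remedy.** With the standard error taken from the likelihood of the observed data, the simulated size at 30% missing is 0.0007 to 0.0012 for r = 0.4 to 0.8, which is nominal within simulation error.

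**Effect on multiplicity.** If all 50 tests were null, the expected number of false positives would be 50 × 0.0103 = 0.5 to 50 × 0.0169 = 0.85. The intended figure is 50 × 0.001 = 0.05, and testing each at 0.05 would give 2.5.

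**The case against.** The strongest objection is that the article never says that values are filled in once or that they are treated as observed. The phrase could be a loose name for full-information likelihood, or for an imputation with a proper variance. In either case there is no inflation. A journal article also commonly leaves the number of imputations and the variance method to a fuller document, and none is shown here.

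Part of this stands. A reader might infer that the plan certainly commits to a single fill-in and that its 0.001 test certainly runs at ten or more times its nominal level. The text does not support that certainty. The single fill-in is the natural reading, not a stated fact. The correlation appears nowhere in the article, and 30% is an allowance for attrition, not a forecast of missingness for each outcome.

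What does not stand is the suggestion that this is only missing detail. The article positively names imputation and pairs it with complete-data tests. Direct likelihood imputes nothing, and classical paired t-tests and repeated measures ANOVA are not how it is normally carried out. No other section of the article corrects the wording.

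**Conclusion.** The concern holds in conditional form. The article specifies an imputation followed by complete-data tests, with nothing that carries imputation uncertainty into the standard errors. Carried out as a single conditional-mean fill-in, under the 30% missingness and correlations of 0.4 to 0.8 assumed above, the 0.001 test runs at about 0.010 to 0.017. The direction is the same in every single-imputation variant checked, but the size depends heavily on the fraction missing.

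A reader might go further and conclude that the multiplicity correction is lost. The figures do not show that. Even at 0.017 each test runs at about a third of 0.05, so the protection is weakened, not removed. If the intention was direct likelihood on the observed data, the type I error is sound and the defect is one of wording, which still needs correcting because an analyst following the text would do something else.

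**What to change.** Remove the imputation step that precedes t-tests and ANOVA, and use one of the following.

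- Preferred: for each outcome, fit a likelihood-based repeated-measures mixed model to all observed values. Test the pre-to-post contrast and, where the outcome is measured at follow-up, the pre-to-6-month contrast from that model.
- Alternative: multiple imputation, with estimates and standard errors combined by Rubin's rules.

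If direct likelihood was already intended, it is enough to say so and to drop the word imputation.

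The cost is about two sentences and standard software, with no new data. Intervals become wider than the single fill-in would report: at 30% missing, by a factor of 1/0.780 = 1.28 at r = 0.4 to 1/0.726 = 1.38 at r = 0.8. This takes nothing from the planned precision, because the sample size was built on 420 observed pairs. At r = 0.6 the direct-likelihood variance of 0.001790 is slightly below that of a paired analysis of those 420, 0.80/420 = 0.001905.

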### Program design

The Life Now Exercise program is a community-based exercise intervention designed to mitigate and rehabilitate the adverse effects of cancer and its treatment and improve physical and psychosocial wellbeing in people with cancer. The mandate of the program is to provide people with cancer access to a cancer-specific exercise program delivered using evidence-based practice. An additional goal of the program is building capacity of exercise physiologists to provide best practice exercise prescription and supervision to people with cancer. Implementation of the program is driven by international guidelines recommending high quality exercise for all people with cancer and the failure of existing resources to engage patients in such behaviour.

The program is administered throughout Western Australia by Cancer Council Western Australia, a state based not-for-profit cancer organisation. Community donations provided to the organisation funds the program which is subsidised for participants so that they can complete the 3-month intervention at no personal financial cost. The program is delivered at a range of community based exercise clinics (typically ~10 per year) that span metropolitan and regional areas of Western Australia. The program operates over three terms per year, catering for up to 150 participants each term (typically ~80–120 participants/term).

A series of elements were developed to support the implementation of the Life Now Exercise program. These include processes for identifying suitable community-based sites, establishing formal agreements with each site, training and supporting exercise physiologists to deliver the program as designed, engaging people with cancer to participate in the program, screening participants to ensure their health status is adequate to exercise safely in the program environment, and program evaluation (Fig. 1). This framework was developed to facilitate sustainable adoption and maximise generalizability beyond a single state-based supportive care program.

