#### Group exercise sessions

Twice weekly exercise sessions are conducted in groups of approximately 10 participants under the supervision of an accredited exercise physiologist. The maximum number of participants per group is 15–20 (site dependent) and the groups are administered with an exercise physiologist to participant ratio of up to 1:10. These sessions are delivered in community based exercise clinics, fitness centres and gym facilities. The sessions last approximately 1 h in duration and consist of a combination of moderate to high intensity aerobic and resistance exercise as well as flexibility exercises. The aerobic exercise component includes 20 to 30 min of at least moderate intensity cardiovascular exercise using a variety of modes such as walking or jogging on a treadmill, cycling or rowing on a stationary ergometer. The target intensity is between 60 to 85% of estimated heart rate maximum. The resistance exercise component involves 6 to 10 exercises that target the major upper and lower body muscle groups (e.g., leg press, leg extension, leg curl, calf raise, chest press, lat pulldown, bicep curl, tricep extension). Target intensity is manipulated from 6 to 12 repetition maximum (RM; i.e., the maximal weight that can be lifted 6 to 12 times which is equivalent to ~60–85% of 1RM) using 1–4 sets per exercise. Resistance exercise selection is individually prescribed. The flexibility component involves approximately 5 min of stretching of the major muscle groups for 15–30 s duration each. Exercise prescription is progressive and modified according to individual response. Session ratings of perceived exertion (RPE) are recorded after the completion of each exercise session to monitor the perceived intensity of the exercise using the 6–20 Borg scale [28]. The target session RPE range is 12–16 [15]. Participants are encouraged to undertake additional home-based aerobic exercise with the goal of achieving a total of at least 150 min of moderate intensity aerobic exercise each week (accumulated through the combination of clinic- and home-based sessions). Participants are provided with a logbook to help monitor their home-based exercise levels but these data are not collected or analysed.

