#### Effectiveness-objective assessments

Objective measurements of physical function, resting blood pressure, height, weight, waist and hip circumferences occurs for all participants at pre- and post-program time points. Physical function is assessed using the 400 metre walk and repeated chair rise tests with lower time taken to complete the tests representing higher functional performance. As a measure of cardiovascular fitness, peak oxygen consumption (VO_2_peak) is estimated from the 400 metre walk test time and heart rate response [32]. A validated oscillometric device or sphygmomanometer is used to record resting brachial blood pressure. Circumferences are measured using a constant tension anthropometric tape in accordance to standard protocols. These assessments are performed in triplicate with the exception of the 400 metre walk test. These assessments are conducted by the same exercise physiologist administering the exercise intervention.

A sub-set of participants willing to attend a tertiary assessment centre complete additional objective assessments to evaluate further components of functional capacity [33]. Involvement in the additional assessments is open to any participant willing to attend an additional testing session and as such, evaluation of these endpoints will be exploratory. Maximal strength of the lower and upper body is determined using the 1RM in the leg press, chest press and seated row exercises. Usual and fast pace 6 metre walks evaluate ambulatory ability while the 6 metre backwards walk is used to assess dynamic balance. Static balance is determined using the sensory organisation test performed on a Neurocom Smart Balancemaster (Neurocom, OR, USA). Body composition and bone health are derived from dual-energy X-ray absorptiometry (DXA; Hologic Discovery A, MA, USA). Regional and whole body lean mass and fat mass as well as trunk adiposity, visceral fat and adipose indices are assessed using whole body DXA scans. Areal bone mineral density of the hip (total hip) and lumbar spine (L_2–4_) as well as whole body bone mineral content is measured by DXA using standard procedures. These assessments are conducted by an independent research assistant not involved with administering the exercise intervention.

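### The sample size takes no account of training in instructor-led groups at several clinics, and no named analysis does; if change varies between groups or sites, precision and power are overstated

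*Protocol article*

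**What the plan says.** Delivery is grouped. Under Group exercise sessions the article states: "Twice weekly exercise sessions are conducted in groups of approximately 10 participants under the supervision of an accredited exercise physiologist". Under Program design it states: "The program is delivered at a range of community based exercise clinics (typically ~10 per year"), and it gives no total for the whole evaluation. For the objective tests done at the clinics, "These assessments are conducted by the same exercise physiologist administering the exercise intervention". The tests on the tertiary-centre sub-set are done by an independent research assistant, and the questionnaires are completed by participants away from the facility.

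Under Statistical analyses, the methods are correlation, chi-square, t-tests and descriptive statistics, and the list ends with "regression and repeated measures ANOVA (or ANCOVA as appropriate) to examine differences over time". Clinically relevant covariates are to be added but are not listed. The required number is given as follows: "420 participants are required to achieve 80% power at an alpha level of 0.001 (two tailed"). The target that this number is meant to detect is printed as a standardised paired change of 0.02. Allowance is made for 30% attrition, which leads to the enrolment figure: "Thus the evaluation will be conducted on a sample size of 600 participants". No ICC or design effect appears.

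**The concern.** People in one group share an instructor, a timetable, a facility and each other for three months. If some groups or clinics produce larger changes than others, change scores within a group or clinic are correlated. A paired t-test or a repeated measures ANOVA on individuals then leaves the between-group and between-site part of the variance out of the standard error of the mean change.

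Two things are at stake. The first is the error rate: the plan chose 0.001 to cover up to 50 tests, and so strict a threshold is sensitive to a standard error that is even slightly too small. The second is the power statement, which has no slack to absorb a design effect.

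**Working it through.** **1. Reproduce the plan's figure.** Inputs from Statistical analyses: two-sided alpha 0.001 (z = 3.2905), power 80% (z = 0.8416), attrition 30%. For paired differences, n = ((3.2905 + 0.8416)/d)² = (4.132/d)².
- Printed d = 0.02: n = 42,687. Power with 420 pairs is about 0.2%.
- d = 0.2: n = 427 by the normal approximation and 433 by the noncentral t. Power with 420 pairs is 79.1% (normal) or 78.3% (t).
- Attrition: 420/0.70 = 600.

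So 420 is a calculation on independent pairs at d = 0.2, with a design effect of 1. Everything below uses d = 0.2, which is not the printed value.

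**2. Formulas for clustering.** With m completers per cluster and ICC the intraclass correlation of the change score:
- design effect DE = 1 + (m − 1) × ICC
- effective n = 420/DE
- power of a test that keeps the 0.001 level: noncentral t with effective n, d = 0.2
- actual alpha of the unadjusted test = 2 × (1 − Φ(3.2905/√DE))
- proportion by which the unadjusted standard error is too small = 1 − 1/√DE

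**3. Assumptions.** The article gives no ICC; 0.01 to 0.05 is assumed. Groups of 10 less 30% attrition leave m = 7. The total number of sites is not given, so two values are assumed: 20 sites (420/20 = 21 completers each) and 10 sites (420/10 = 42 each).

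**4. Results.**

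| Clustering | ICC | DE | Effective n | Power | Actual alpha | SE too small by |
|---|---|---|---|---|---|---|
| None | 0 | 1.00 | 420 | 78% | 0.001 | 0% |
| Group, m = 7 | 0.01 | 1.06 | 396 | 75% | 0.0014 | 3% |
| Group, m = 7 | 0.05 | 1.30 | 323 | 61% | 0.004 | 12% |
| 20 sites, m = 21 | 0.01 | 1.20 | 350 | 66% | 0.003 | 9% |
| 20 sites, m = 21 | 0.05 | 2.00 | 210 | 33% | 0.02 | 29% |
| 10 sites, m = 42 | 0.01 | 1.41 | 298 | 55% | 0.006 | 16% |
| 10 sites, m = 42 | 0.02 | 1.82 | 231 | 39% | 0.015 | 26% |
| 10 sites, m = 42 | 0.05 | 3.05 | 138 | 16% | 0.06 | 43% |

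The last three columns belong to different choices of test. The unadjusted test pays in error rate; a test that holds 0.001 pays in power.

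**5. Detectable effect** at 420 completers and 80% power, d = 4.132/√(420/DE): 0.20 at DE 1, 0.23 at DE 1.30, 0.27 at DE 1.82.

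**The case against.** The case on the other side has real substance.

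- **The harm is conditional.** It needs a positive ICC of the change score, and the article gives none. Stable differences between sites, assessors or devices cancel in a pre-post difference, and a benefit of group support common to all groups moves the mean without creating correlation. Instructors take one training course, their compliance is monitored, and prescription is individualised, all of which could keep the ICC small. This stands. A reader might infer that the standard errors are certainly too small; the documents support that only if change differs between groups or sites. The Discussion names social support and the group setting as possible influences on adherence and motivation. That makes such differences plausible but does not establish them.
- **The analysis list is open-ended.** It says what analyses will include, and an analysis plan not shown could add a cluster term. This also stands. A reader might infer that the plan rules out a site or group effect; it does not. The sample-size half of the point is firmer, because there the article gives a complete calculation with a result.
- **Ten sites is a yearly figure.** Collection began in 2011 and runs until 600 are recruited, so reading it as ten sites in all is not supported. The ten-site rows are one scenario.
- **Instructor testing is limited.** It covers the clinic objective tests only. For the questionnaires and sub-set tests, any correlation would come from the shared group and instructor. The article already lists assessor bias as a limitation.
- **Clustering is not the first reason the stated power fails.** At the printed d = 0.02, 420 pairs have almost no power even with full independence.

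**Conclusion.** The point holds in conditional form. The design groups participants, the figure of 420 has no allowance for that, and no method named in the article allows for it. If change scores vary between groups or sites, following the plan as written gives intervals that are too narrow, an error rate above 0.001, and less power than stated.

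At group level, over the assumed ICC range, the loss is modest to material: power falls from 78% to between 75% and 61%, and the error rate rises to between 1.4 and 4 times nominal. At site level it could be much larger, but those figures depend on a number of sites that the article does not give. At ICC 0 the plan is unaffected. All power figures assume that the intended effect size is 0.2.

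**What to change.** 1. Reconcile d = 0.02 with 420 before anything else.
2. Analyse change with a mixed model that has random effects for site and for group (site by term), with small-sample degrees of freedom such as Kenward-Roger or Satterthwaite. Cluster-robust errors with a small-cluster correction are an alternative.
3. Make sure that site and group membership are kept in the evaluation dataset. The article does not say that they are.
4. Report the estimated ICC for each main outcome.
5. Replace the power sentence with a short table of power or detectable d over ICC 0 to 0.05, once d is settled and the number of sites is known.

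The cost is analysis code, a check on data fields and a rewritten power sentence, without enrolling more participants. The downside is wider intervals and a less favourable power figure.
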